## 2 Summary

|                                   |                                                                                                                                                                                                                                                                                                                                                                                                                                                                                                                                                                                                                                                                                                                                    |
|-----------------------------------|------------------------------------------------------------------------------------------------------------------------------------------------------------------------------------------------------------------------------------------------------------------------------------------------------------------------------------------------------------------------------------------------------------------------------------------------------------------------------------------------------------------------------------------------------------------------------------------------------------------------------------------------------------------------------------------------------------------------------------|
| Title                      | Staging laparoscopy combined with ultrasonography and near-infrared fluorescence imaging to detect occult pancreatic metastases                                                                                                                                                                                                                                                                                                                                                                                                                                                                                                                                                                                                    |
| Trial design               | A phase II single center, single-arm trial to assess the added value of staging laparoscopy (SL), laparoscopic ultrasonography (LUS) and near-infrared (NIR) fluorescence imaging in patients with pancreatic cancer undergoing resection with curative intent.                                                                                                                                                                                                                                                                                                                                                                                                                                                                    |
| Rationale                  | Even after extensive preoperative assessment, up to 38% of patients undergoing laparotomy with curative intent turn out to have metastases or unresectable disease, preventing curative surgery. Moreover, a substantial number of patients present shortly after surgery with liver metastases that must have been present during surgery, but have not been identified. SL combined with LUS and NIR fluorescence imaging may identify metastases and unresectable disease, sparing patients with incurable disease the morbidity, inconvenience and expense of a futile operation. Staging laparoscopy in pancreatic cancer patients is being advocated in literature, but has not yet been implemented in clinical guidelines. |
| Main objective             | The main objective of this study is to determine the added value of SL, LUS and NIR fluorescence imaging in patients with pancreatic cancer undergoing resection with curative intent and to identify predictors for patients that may benefit from SL.                                                                                                                                                                                                                                                                                                                                                                                                                                                                            |
| Endpoints                  | 
 
- Distant disease-free survival
 
- Overall survival
 
- Percentage of averted laparotomies.
 
- Percentage of averted resections.
 
- Duration of surgical procedures.
 
- Perioperative morbidity and mortality.
 
- Sensitivity of LUS vs. NIR fluorescence imaging.
 
- Positive predictive value of IOUS vs. NIR fluorescence imaging.
 
- Stratification of malignant lesions detected only by NIR fluorescence imaging.
 
                                                                                                                                                                                           |
| Patient selection criteria | 
Inclusion criteria:
 
 
- 18 years or older
 
- All patients with pancreatic or periampullary cancer undergoing resection with curative intent.
 
- Absence of any psychological, familial sociological or geographical condition potentially hampering compliance with the study protocol and follow-up schedule; those conditions should be discussed with the patient before
 
                                                                                                                                                                                                                                                                                 |

|                                    |                                                                                                                                                                                                                                                                                                                                                                                                                                                                                                               |
|------------------------------------|---------------------------------------------------------------------------------------------------------------------------------------------------------------------------------------------------------------------------------------------------------------------------------------------------------------------------------------------------------------------------------------------------------------------------------------------------------------------------------------------------------------|
|                                    | 
registration in the trial;
 
 
- Before patient registration, written consent must be given according to ICH/GCP, national and local regulations.
 
 
Exclusion criteria:
 
 
- History of allergy to iodine, shellfish or ICG;
 
- Pregnant or lactating woman;
 
- Any condition that in the opinion of the investigator could potentially jeopardize the health status of the patient.
 
 |
| Planned trial interventions | 
In addition to standard-of-care, patients will receive an intravenous injection of 10 mg ICG 24 prior to surgery. During surgery, patients undergo a SL, whereupon inspection, LUS and NIR fluorescence imaging will be performed. A biopsy will be taken from any suspect lesions. Decision to continue the resection is up to the surgeon. Follow-up will last at least 6 months.
                                                                                                                    |
| Statistical design          | 
Using A'Hern's single stage phase II trial design and <math>\alpha=0.05</math> and power=80%, 25 patients are needed to distinguish between an averted laparotomy rate of 30% (worth exploring in a phase III trial) and 10% or less (unacceptable outcome). Therefore, a total of 25 patients will be included. This requires at least 6 averted laparotomies to reach the positive endpoint.
                                                                                                         |

### 3 Background

Pancreatic cancer has a very dismal prognosis. Surgery offers the sole chance of long-term survival. However, the presence of metastatic disease in pancreatic cancer patients limits surgical interventions. Even after extensive preoperative assessment, up to 38% of patients undergoing laparotomy with curative intent turn out to have incurable disease, for example due to metastases or an unresectable primary tumor (1). All current preoperative imaging modalities, including CT and MRI, have limited sensitivity in detecting the typically very small peritoneal implants and superficial liver metastases of pancreatic cancer. In a disease with such a poor prognosis, it is important to spare patients with incurable disease the morbidity, inconvenience and expense of a futile operation. Therefore, staging laparoscopy (SL) is being advocated in literature in selected patients (2). However, it has not yet been implemented in clinical guidelines; each individual surgeon has to apply his or her threshold as to whether SL is indicated. One of the aims of this study is to design a clinical protocol for SL that fits in the clinical pathway of patients with pancreatic and periampullary cancer.

The yield of SL depends on the quality of preoperative imaging and the inherent likelihood of metastatic disease (3). In addition, sensitivity of SL can be amplified by adding laparoscopic ultrasonography (LUS) and near-infrared (NIR) fluorescence imaging (4). When no metastatic lesions are found, ultrasonic examination of the whole liver, lymph nodes and superior mesenteric artery can be readily performed. NIR fluorescence imaging using indocyanine green (ICG) is a relatively easy method that can be used to identify metastases in the liver. The hepatic clearance of ICG enable identification of liver tumors, but do not allow detection of metastases located elsewhere. Yokoyama et al. have shown that NIR fluorescence imaging during open surgery identified micrometastases in the liver in 16% (8 of 49) of patients with pancreatic cancer (5). Importantly, abnormal fluorescence of at least 1.5 mm in greatest diameter was highly predictive for manifestation of hepatic metastases within 6 months: 77% (10 of 13) of patients developed hepatic metastases, compared to 3%

(1 of 36) of patients without abnormal fluorescent lesions. Our group showed feasibility of NIR fluorescence imaging of colorectal cancer liver metastases during open surgery (6) and of uveal melanoma liver metastases during laparoscopic procedures (7).

Presently, the only blood-based biomarkers for diagnosis, prognosis and monitoring of treatment in pancreatic patients are measurements of carbohydrate antigen 19-9 (CA19-9) and carcinoembryonic antigen (CEA), but these are not very specific (8). Circulating tumor cells (CTCs) are cells that have detached from the primary tumor, entered the blood circulation and may lead to distant metastases (9). Characterization of CTCs, including analyzing KRAS mutations, may result in further insight into the clinical implications of CTC detection in pancreatic cancer patients.

This study will be the first to combine SL, LUS and NIR fluorescence imaging and aims to determine the added value of these three imaging techniques in patients with pancreatic and periampullary cancer undergoing resection with curative intent. In addition, we aim to identify predictors for patients that may benefit from SL and to design a clinical protocol for SL that fits in the clinical pathway.

#### **4 Study design**

All patients planned to undergo explorative or curative surgery for pancreatic or periampullary cancer can be included, provided that they meet the inclusion criteria and none of the exclusion criteria. All patients will receive standard-of-care. This includes a CT-scan < 1 month prior to surgery. Optional imaging, such as (endoscopic) ultrasonography, MRI and FDG-PET, may also be performed if required. In addition, peripheral blood samples (8 mL) will be taken from patients before surgery or chemotherapy. These samples will be analyzed for CTCs, CEA, CA19-9 and bilirubin levels. Patients will receive up to three days before surgery an intravenous injection of 4 ml 2.5 mg/ml ICG (10 mg ICG in total).

The SL procedure starts with visual inspection. The laparoscope is inserted via a subumbilical 10 mm trocar. A second 10 mm port is inserted along the anticipated laparotomy incision to allow LUS under direct vision. Up to two additional 5 mm ports may be necessary to allow exposure of organs and potential palliative surgery. The whole abdomen is inspected, including the parietal and visceral peritoneum, the pelvis, the liver, the porta hepatitis, the gastrohepatic omentum, the duodenum, the transverse mesocolon and celiac region. Secondly, LUS (with or without Doppler) of the primary tumor, liver, portal vein, hepatic artery, lymph nodes and superior mesenteric artery will be performed. NIR fluorescence imaging of the liver surface will be performed lastly. Fluorescence will be divided into rim, partial, full and nonspecific (i.e. artefacts) pattern. Any lesions likely to be metastases are sampled and analyzed, either via a biopsy or via radical resection. In case of multiple lesions with similar appearance on inspection, ultrasound and fluorescence, only one biopsy has to be performed when LUS shows a similar signal in all these lesions. However, when one or more lesions are found solely by NIR fluorescence imaging, multiple small biopsies have to be performed to confirm the diagnosis.

In case no metastases are identified, the surgical procedure will continue, either laparoscopic or via laparotomy. In the validation phase of the laparoscopic fluorescence, the liver will be assessed again with the validated open fluorescence imaging system once the laparotomy has been performed (6). When metastases are identified, the decision to continue the resection of the primary tumor is up to the surgeon. When only NIR fluorescence imaging identifies one or more metastases, the procedure will continue, as the clinical significance of these lesions is yet unknown. Reference for final diagnosis of lesions will be histopathological examination at the pathology department. Furthermore, ascetic fluid will be collected in 3 regions: near the duodenum, the ligament of Treitz and the cavum of Douglas. These samples will be analyzed for tumor cells, similar to the EXPECT study.

Follow-up will occur according to the current local standard protocol, including a visit every three months to the outpatient clinic of surgery in conjunction with the department of oncology. Visit. In short, this includes an outpatient visit to the clinic of surgery every three months. A CT-scan will be performed only in case locoregional or metastatic disease is suspected. Radiologic findings, hematology (e.g. CTCs CA19-9, CEA-mRNA levels), pathology, ascetic fluid etc. will be collected to identify predictors for patients who may benefit from SL.

Risk stratification will be done by stage groups of the tumor and CA19-9 levels.

[figure not shown]

**Figure 1.** Flow diagram of study. LUS: laparoscopic ultrasonography; PA: pathology; RFA: radiofrequency ablation; CT: computed tomography.

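### The continuation rule in Section 4 turns only on metastases, although the stated purpose also includes sparing patients with unresectable disease a futile operation

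*Protocol*

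**What the plan says.** Section 4 of the protocol gives three rules for what follows the staging laparoscopy:

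- No metastases: "In case no metastases are identified, the surgical procedure will continue, either laparoscopic or via laparotomy".
- Metastases: "When metastases are identified, the decision to continue the resection of the primary tumor is up to the surgeon".
- Metastases seen on NIR imaging alone: "When only NIR fluorescence imaging identifies one or more metastases, the procedure will continue".

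The Summary (Rationale) sets a wider purpose: "SL combined with LUS and NIR fluorescence imaging may identify metastases and unresectable disease, sparing patients with incurable disease" a futile operation. Section 3 describes the incurable disease found at laparotomy as arising "for example due to metastases or an unresectable primary tumor". Section 4 itself requires LUS "of the primary tumor, liver, portal vein, hepatic artery, lymph nodes and superior mesenteric artery will be performed".

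The Summary (Planned trial interventions) condenses the decision to: "A biopsy will be taken from any suspect lesions. Decision to continue the resection is up to the surgeon".

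The main objective (Section 5.1) is a lower laparotomy rate. The only main outcome (Section 6.1) is the percentage of averted laparotomies. Section 7 calls the trial positive at six or more among 25 patients.

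**The concern.** The protocol has LUS look at local resectability, but the Section 4 text gives that information no part in the decision. A patient with a tumor that LUS shows to be unresectable, and with no metastases, falls under the first rule, and that rule is worded as mandatory.

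The continuation rule decides who can become an event for the main outcome. If such a patient is opened because the rule says to continue, the laparotomy was not averted, although it is of the kind the rationale hopes to prevent. The count could then understate what the combined procedure can achieve. The gap would also carry over into the clinical protocol for staging laparoscopy that Section 5.2 sets as a secondary objective. A rule for decisions during the operation belongs in the protocol, so this is not a detail that an analysis plan would be expected to supply.

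**Working it through.** **1. The plan's own figure.** Inputs from Section 7: n = 25, success if X ≥ 6, unacceptable rate 10%, target rate 30%, α = 0.05, power 80%. With X binomial:

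- P(X ≥ 6 | n = 25, p = 0.10) = 0.0334, below 0.05.
- P(X ≥ 6 | n = 25, p = 0.30) = 0.8065, above 0.80.

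A search over n = 15 to 34 finds no smaller n that meets both limits. The design reproduces, and nothing in this point disturbs it.

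**2. The findings set against the Section 4 text.**

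| Finding at laparoscopy | What the Section 4 text says | What the rationale implies |
|---|---|---|
| No metastases, resectable | Continue | Continue |
| Metastases | Surgeon decides | Futile operation may be spared |
| Metastases on NIR only | Continue, significance unknown | Left open by design |
| No metastases, unresectable on LUS | Continue (first rule, no exception) | Futile operation may be spared |

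Only the last row conflicts. The first rule sends the patient on; the rationale would have the patient spared.

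**3. Does the Summary line settle it?** There are two readings. In the narrow one, the line follows directly on the biopsy of suspect lesions and is a short form of the second rule in Section 4; it then says nothing about local unresectability. In the broad one, the surgeon may stop for any reason; it then contradicts the unconditional instruction in Section 4 to continue when there are no metastases. Under either reading the Section 4 sentence needs amending.

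**4. Can the effect be sized?** At the target rate, 25 × 0.30 = 7.5 averted laparotomies are expected. Let s be the share of these that would come from local unresectability alone, and o the fraction of such patients who are opened despite the LUS finding. The countable rate would then be 0.30 × (1 − s × o). This needs three things the protocol does not give:

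- s. The figure of up to 38% in Sections 2 and 3 pools metastases and unresectable disease without a split.
- o. It depends on how surgeons read the text.
- Whether the 30% target was meant to include local-only cases at all. Section 7 does not say how it is composed.

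If s = 0 or o = 0, the countable rate is 0.30 × (1 − 0) = 0.30 and nothing is lost. Only the direction is fixed: compared with a rule that lets the surgeon stop, the literal rule can lower the count but cannot raise it. It therefore cannot increase the chance of a false positive result.

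**The case against.** The strongest defense has four parts.

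- **The Summary already leaves the decision to the surgeon.** The line closes a description of the whole procedure and names no condition. This is a fair reading, but it then conflicts with Section 4, so it does not remove the need to amend.
- **Figure 1 is not shown.** Its caption defines radiofrequency ablation, which appears nowhere else in the text at hand, so the flow diagram probably has branches that the prose omits. This stands: the point is confined to the prose. If the figure has the branch, the prose should match it.
- **To continue is not necessarily to open.** Section 4 allows a laparoscopic continuation and adds: "Up to two additional 5 mm ports may be necessary to allow exposure of organs and potential palliative surgery". A patient judged unresectable could have laparoscopic palliation and still avoid laparotomy. This stands as well and limits the effect, but neither sentence says what to do on an LUS finding of unresectability.
- **A rule tied to metastases can be defended.** The title speaks of occult metastases, histopathology is the reference for lesions, and no reference is given for vessel involvement judged by LUS. That argues against an automatic stop. It does not argue against letting the surgeon decide.

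A reader might go further and infer that the trial loses a calculable amount of power. The documents do not support this, because none of the three quantities under step 4 is given. A reader might also infer that the protocol forces a laparotomy on unresectable patients; the laparoscopic option rules that out. Nor does the main outcome exclude laparotomies averted for local reasons: the wording in Section 6.1 counts them whatever the cause.

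**Conclusion.** The point holds as a mismatch between the decision rule in the Section 4 text and the protocol's stated purpose. Read literally, the rule sends a patient who is locally unresectable on LUS, without metastases, on to surgery; if that patient is opened, the case cannot count toward the six needed. The Summary does not cure this.

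The size is unknown and may be zero, so no power figure should be attached. The conclusion rests on the prose being followed as written and on Figure 1 not already providing the branch. The fault lies in the decision rule; the endpoint, cut-off and sample size calculation are sound on this point. It should be corrected, with medium confidence.

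**What to change.** Amend the Section 4 rule so that surgery continues when neither metastases nor unresectable disease is identified, and so that the surgeon decides when either is found. Keep the rule that patients with lesions seen only on NIR imaging continue. Align the Summary line and, if needed, Figure 1 with this wording. Reporting averted laparotomies by cause (metastases or local unresectability) would be useful but is optional.

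The cost is one amended sentence. The 25 patients, the cut-off of six, and Sections 6.1 and 7 stay unchanged. The downside is clinical: a false-positive LUS judgment of unresectability could cost a patient a resection. Leaving the decision to the surgeon, and not making the stop automatic, limits that risk.

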## **5 Objectives**

### **5.1 Main objective**

- To determine if SL, LUS and NIR fluorescence imaging can reduce the laparotomy rate in patients with pancreatic or periampullary cancer planned to undergo resection with curative intent.

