## **6 Outcomes**

### **6.1 Main outcomes**

- Percentage of averted laparotomies.

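### Metastases found only by NIR never stop the operation, so the averted-laparotomy outcome cannot show the NIR part of the main objective

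*Protocol*

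**What the plan says.** The main objective (Protocol section 5.1) is "To determine if SL, LUS and NIR fluorescence imaging can reduce the laparotomy rate". Section 6.1 lists one main outcome, "Percentage of averted laparotomies". Section 7 sets 25 patients, an uninteresting rate of 10% or less, a target rate of 30%, and success at 6 or more averted laparotomies.

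Section 4 fixes the order of the techniques: visual inspection, then LUS, and "NIR fluorescence imaging of the liver surface will be performed lastly". It gives two continuation rules. The general one is "When metastases are identified, the decision to continue the resection of the primary tumor is up to the surgeon". The one for NIR-only findings is "When only NIR fluorescence imaging identifies one or more metastases, the procedure will continue, as the clinical significance of these lesions is yet unknown". Section 4 also requires that "when one or more lesions are found solely by NIR fluorescence imaging, multiple small biopsies have to be performed to confirm the diagnosis", but no text lets a positive biopsy change the NIR-only rule.

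The Summary, under planned interventions, gives only the general rule: "Decision to continue the resection is up to the surgeon".

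**The concern.** The objective credits three techniques with a possible reduction in laparotomies. The outcome can record a reduction only where the operation is stopped, and section 4 rules out stopping for NIR findings alone. Those are the patients in whom NIR adds something that inspection and LUS did not show.

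What is at stake is the conclusion. A count of 6 or more could be reported as support for taking the three-part package to a phase III trial, although the count was produced by inspection and LUS. A count below 6 could be held against a package whose third part had no means of raising it.

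**Working it through.** **1. The plan's own design.** Inputs from section 7: n = 25, cut-off 6, p0 = 0.10, p1 = 0.30, alpha 0.05, power 80%. With X binomial(25, p), the probability of success is

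P(X ≥ 6 | p) = 1 − Σ(k = 0 to 5) C(25, k) p^k (1 − p)^(25 − k).

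- p = 0.10: 0.0334 (exact one-sided alpha, below 0.05)
- p = 0.30: 0.8065 (power, above 0.80)

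Taking for each n the smallest cut-off with alpha ≤ 0.05, n = 24 (cut-off 6) has power 0.771. In a search over n = 15 to 39, n = 25 is the first to reach 0.80. The stated design is reproduced and is not at fault.

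**2. Which patients can enter the count.** Patients fall into three groups under the section 4 rules:

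| Finding | Rule in section 4 | Can NIR add an averted laparotomy? |
|---|---|---|
| Metastases on inspection or LUS, with or without NIR | Surgeon decides | Not separately. Extra NIR lesions may sway the decision, but a single-arm percentage cannot attribute this to NIR |
| Metastases on NIR only | Procedure continues | No, by rule |
| No metastases on any technique | Procedure continues | No |

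The expected number averted because of detected metastases is therefore 25 × q × c. Here q is the probability that inspection or LUS shows metastases, and c is the probability that the surgeon then stops. The probability of an NIR-only finding does not appear. NIR could enter only through c, in patients already positive on another technique.

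Section 4 allows continuation by laparoscopy as well as by laparotomy. If a laparoscopic continuation were counted as an averted laparotomy, that would not be due to NIR either, so the conclusion is unchanged.

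**3. Whether power is affected.** This depends on what the 30% stands for, and section 7 does not split it by technique. Suppose, as an assumption, that d percentage points of the 30% were expected from NIR-only patients. The reachable rate is then 30% − d:

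| d (points) | Reachable rate | P(X ≥ 6) |
|---|---|---|
| 0 | 30% | 80.7% |
| 5 | 25% | 62.2% |
| 10 | 20% | 38.3% |
| 16.3 (8/49) | 13.7% | 11.6% |

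The last row is an outer bound. Section 3 reports that NIR in open surgery "identified micrometastases in the liver in 16% (8 of 49) of patients with pancreatic cancer", but does not say how many of the 8 would have been missed by inspection and LUS.

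**The case against.** The best defence is that the NIR-only rule is deliberate and reasoned: the significance of such lesions is unknown, so the protocol declines to act on them and studies them elsewhere. The Summary lists an endpoint on malignant lesions seen only by NIR. Section 6.2 covers sensitivity and positive predictive value against histopathology, and predictive values for later distant metastases. All of this stands, and it means NIR is not left unassessed. It does not mend a main objective that claims a laparotomy effect for NIR.

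A reader might infer that the trial is underpowered. The documents do not support that. No passage places NIR-only patients inside the 30%, and a target for averted laparotomies in a protocol that excludes such patients is most naturally read as d = 0. Section 3 also cites up to 38% of patients with incurable disease at laparotomy, without tying that figure to NIR, so a 30% target does not need NIR.

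A reader might also say that NIR can never influence the main outcome. That is exact only for patients negative on inspection and LUS.

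Finally, the Summary and section 4 could be called contradictory. Section 4 itself states the general rule and then the exception, so the Summary reads more as a shortened version that drops the exception. The flow diagram is not available to settle it. The two passages still differ on a point that affects what is counted.

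**Conclusion.** The concern holds as a mismatch between objective and outcome. NIR-only patients contribute 0 of 25 to the main outcome by rule, so the 6-of-25 decision concerns inspection plus LUS. Reaching 6 would not show that NIR helped, and falling short would not count against NIR's added detection.

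This rests on the section 4 rule being followed as written and on no text linking a positive biopsy to stopping. It does not rest on any power loss: exact alpha is 0.033, and power stays at 80.7% unless the sponsor meant part of the 30% to come from NIR-only findings. The point should be fixed because it changes what the result may be said to show. It does not invalidate the design or the sample size.

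**What to change.** 1. Restate the main objective (5.1), main outcome (6.1) and section 7, with the matching Summary rows, so that the averted-laparotomy rate, the 30% target and the 6-of-25 rule refer to inspection plus LUS under the section 4 rule. If part of the 30% was meant to come from NIR-only patients, say so and recompute the power.
2. Assess NIR through the outcomes already listed in the Summary and section 6.2.
3. Add one pre-specified descriptive count: patients out of 25 who are negative on inspection and LUS and have a histologically confirmed liver metastasis found by NIR only, with an exact 95% confidence interval. Restricting it to patients negative on both avoids including anyone who may already count as averted. Report it apart from the 6, and do not label these patients as averted while the protocol calls the significance unknown. The interval will be wide: with 0 of 25 its upper limit is 1 − 0.025^(1/25) = 13.7%.
4. Reconcile the Summary with section 4 on continuation when only NIR is positive. Which clinical rule applies is for the sponsor and investigators to decide.

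The cost is protocol wording and one descriptive analysis from biopsies and pathology already planned, with no added patients or procedures. The drawback is that the headline claim narrows to staging laparoscopy with LUS.
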